### **8.3. Exploratory Efficacy Analyses**

Descriptive analyses will be provided only.

#### **8.3.1. Days free of organ support (respiratory, renal and vasopressor)**

The number of days free of organ support (respiratory, renal and vasopressor) will be calculated as the total number of calendar days from treatment start up (Day 1) to Day 28, when a patient is alive and does not require any organ support. If a patient died on or before Day 28, the number of days will be set to 0. For patients withdrawn alive before Day 28, number of days will be calculated until day of withdrawal. The mean, median, Q1 and Q3, min and max of the distribution of the number of days free of organ support will be provided by treatment group overall and by baseline clinical status.

#### **Subgroup analyses :**

Days free of organ support will be described by baseline sTREM-1 level (above or equal to the median vs below).

#### **8.3.2. Respiratory support type**

The number and percentage of patients under each kind of ventilation at Day 28 and the number and percentage of patients under invasive mechanical ventilation at Day 28 and Day 60 will be described by treatment overall and by baseline clinical status.

The following categories of mechanical ventilation are considered invasive:

- Ventilation requiring intubation
- ECMO
- Extracorporeal CO2 clearance

The following categories of mechanical ventilation are considered non-invasive:

- Non-invasive ventilation
- High flow

Patients who died or are lost to follow-up before Day 28 or before Day 60 will be excluded from these summary tables.

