### 3.3.2. Other Secondary efficacy and safety endpoints

- Clinical status as improvement from baseline (Yes vs No) at Day 28 and Day 60
- Clinical status as a 3-point ordinal scale (change from baseline categorized as improved, unchanged, worsened) at Day 28 and Day 60
- All-cause mortality on day 28 and day 60
- Days free of organ support (respiratory, renal and vasopressor) at Day 28
- Respiratory support type at Day 28 and Day 60
- Safety laboratory tests (as part of routine clinical care): hematology, coagulation, plasma biochemistry
- Adverse events (AEs), serious adverse events (SAEs) and deaths
- Suspected adverse drug reactions (serious and non-serious)
- Secondary infections
- Hospital free survival (the proportion of patients alive and not hospitalized on day 28)
- Sustained improvement (The proportion of patients alive and not hospitalized on day 60)
- Alive and free of respiratory support at Day 28 and Day 60

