## 4. General Statistical Considerations

### 4.1. Tabulations and Presentations

All summaries and results in Tables, Listings and Figures (TLFs) should be presented for the following treatment groups:

| Treatment groups                                                  | Label in TLFs           |
|-------------------------------------------------------------------|-------------------------|
| 1.0 mg/kg/h continuous intravenous (i.v.) infusion of nangibotide | Nangibotide 1.0 mg/kg/h |
| Matching placebo                                                  | Placebo                 |

Continuous data will be described using descriptive statistics (i.e. n, mean, standard deviation, median, interquartile range (IQR), minimum, and maximum). Categorical data will be described using the patient count and percentage in each category. For the summary statistics of all numerical variables unless otherwise specified, minimum and maximum will be displayed to the same level of precision as reported. Mean, median and IQR will be displayed to one level of precision greater than the data collected. Standard deviation will be displayed to two levels of precision greater than the data collected.

When count data are presented, the percentage will be suppressed when the count is zero in order to draw attention to the non-zero counts. A row denoted “Missing” will be included in count tabulations where specified on the shells to account for dropouts and missing values. The denominator for all percentages will be the number of patients in that treatment within

the Analysis Set of interest, unless otherwise specified. Percentages will be presented to one decimal place.

Any imputed data will be used in summary tables and figures and the original collected data will be displayed in listings. Data will be displayed in all listings sorted by treatment group. Patients will be identified in the listings by the patient identification number concatenated with the investigator number.

Two-sided p-values will be displayed except for the primary analysis of clinical status (7-point ordinal scale) at Day 28.

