### 8.1. Analysis of the Primary Endpoint of Part 2: Clinical Status

The clinical status (7-point ordinal scale) at Day 28 will be compared between treatment group using a CMH stratified by baseline clinical status. At baseline, patients are hospitalized on invasive mechanical ventilation or ECMO (Clinical status = 6) or hospitalized, on non-invasive ventilation or high flow oxygen devices (Clinical status = 5).

Patients with a missing clinical status at Day 28 visit and who died prior to or on Day 28 will be assigned the category of 7 at Day 28. Patients with a missing clinical status at Day 28 visit and without documented death occurring prior to or on Day 28 will be assigned the last available clinical status.

The distribution (counts and percentages) of the 7-point ordinal scale will be displayed by treatment group and baseline level (5 or 6) (i.e., the 2x2x7 contingency table).

The 7-point ordinal scale will be compared between treatment groups using a Cochran-Mantel-Haenszel test stratified by baseline clinical status (5 or 6) using modified ridit scores. The Wald test one-sided p-value for the difference in raw mean scores will be provided.

The same analysis will be conducted in patients with a sTREM-1 above the median value at baseline vs below.

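### Respiratory support type is described only among survivors with known status, so the arms are not comparable if mortality differs; the gap that matters is invasive ventilation at Day 60

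*SAP*

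**What the plan says.** Section 3.3.2 of the SAP lists "Respiratory support type at Day 28 and Day 60" among the other secondary endpoints. Section 8.3.2 gives each kind of ventilation at Day 28 and adds that "the number and percentage of patients under invasive mechanical ventilation at Day 28 and Day 60 will be described by treatment overall". The results are also split by status at entry (5 or 6), and the subgroup paragraph repeats the description by baseline sTREM-1 level. The section closes with the rule at issue: "Patients who died or are lost to follow-up before Day 28 or before Day 60 will be excluded from these summary tables".

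This departs from the general rule in Section 4.1, "The denominator for all percentages will be the number of patients in that treatment within" the analysis set unless otherwise specified, and no reason is given. It also differs from how the SAP treats death elsewhere:

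- Primary scale (Section 8.1): patients with a missing Day 28 status "who died prior to or on Day 28 will be assigned the category of 7 at Day 28".
- Organ-support-free days (Section 8.3.1): "If a patient died on or before Day 28, the number of days will be set to 0".
- Alive and free of respiratory support (Section 8.3.5): a death does not meet the endpoint, and there is an explicit unknown class.
- PaO2/FiO2 categories (SAP Addendum, Section 3.5): death is grouped with worsening.

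Section 8.3 limits the whole block to description: "Descriptive analyses will be provided only".

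**The concern.** Survival is an outcome after randomisation. Once deaths are removed, the two columns compare whoever happened to survive in each arm, and randomisation no longer makes those groups alike. If one arm has fewer deaths, its extra survivors enter its denominator and perhaps its numerator, while their counterparts in the other arm are absent. The percentage on invasive ventilation can then differ between arms only because mortality differs. The same applies within each sTREM-1 subgroup.

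The exclusion is also loosely worded. It names both visits in one clause, so it does not say whether a patient who dies between Day 28 and Day 60 stays in the Day 28 table.

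**Working it through.** The SAP states no figure for this table, so there is none to reproduce. The check is the direction and size of the shift.

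**Inputs.** From the SAP: deaths and losses are excluded; all patients enter at clinical status 5 or 6, so all have ventilatory support at baseline (Section 8.1). The SAP gives no mortality rate and no rate of ventilation at follow-up, so these are assumed and varied.

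**Formula.** Take n patients, d deaths, v survivors on invasive ventilation, x deaths averted, and a share f of those x still on invasive ventilation at the visit.

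- Survivor-only percentage: v/(n−d) becomes (v + f·x)/(n−d+x).
- It rises only if f > v/(n−d), that is, if the extra survivors are ventilated more often than the other survivors.
- Dead or invasively ventilated, over all patients: (d+v)/n becomes (d−x+v+f·x)/n.

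**Main illustration** (n = 100, d = 30, v = 10, x = 5). Reference: 10/70 = 14.3% among survivors; (30+10)/100 = 40% dead or invasively ventilated. The threshold for f is 14.3%.

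| Of the 5 extra survivors, still ventilated | Survivor-only | Dead or invasive, all patients |
|---|---|---|
| 0 | 10/75 = 13.3% | 35% |
| 1 | 11/75 = 14.7% | 36% |
| 2 | 12/75 = 16.0% | 37% |
| 5 | 15/75 = 20.0% | 40% |

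With 1 or 2 of the 5 still ventilated, the survivor-only figure moves unfavourably while the all-patient figure improves.

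**Range** (n = 100, x = 10), survivor-only percentage:

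| d / v | Reference (= threshold for f) | f = 0 | f = 0.25 | f = 1 |
|---|---|---|---|---|
| 20 / 10 | 12.5% | 11.1% | 13.9% | 22.2% |
| 30 / 15 | 21.4% | 18.75% | 21.9% | 31.25% |
| 40 / 20 | 33.3% | 28.6% | 32.1% | 42.9% |

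The figure falls in every row at f = 0, rises in every row at f = 1, and goes either way at f = 0.25.

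**Restoring deaths to the denominator is not enough.** In the main illustration with all 5 still ventilated, invasive ventilation over all patients still goes from 10/100 = 10% to 15/100 = 15%. Death needs its own row.

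**What other tables cover.** At Day 28, Section 8.1 displays all seven categories by arm and baseline level. It also tests the ≤5 versus >5 split, with odds ratios, overall and by sTREM-1 level. Status 6 is invasive ventilation or ECMO and 7 is death, so >5 is dead or invasively ventilated. At Day 60, Section 8.2 repeats mortality and Section 8.3.5 reports alive and free of any respiratory support, which does not separate invasive from other support. The Addendum (Section 3.4) adds clinical status only for Day 1 to Day 14.

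**Day 60 denominator.** The schedule in Section 11.1 restricts Day 60 follow-up to parts 2 and 3. With 220 patients enrolled and 60 in part 1, at most 220 − 60 = 160 have a planned Day 60 visit. Section 8.3.2 does not say so.

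**The case against.** The strongest reply is that nothing is inferred from this table. It is descriptive, with no test or estimate, and type of support among patients alive with known status is a legitimate description. Section 8.2 reports alive, dead and lost by arm, and Section 8.3.2 gives counts as well as percentages, so a careful reader can set them side by side. At Day 28 the composite that keeps deaths in is already analysed. All of this stands, and it keeps the point modest.

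For Day 60 the reply is weaker. Section 3.3.2 lists a three-category change from baseline at Day 60. If tabulated by baseline level, it would let one rebuild dead or invasively ventilated: worsened among those starting at 5, not improved among those starting at 6. But Section 8.1 specifies that table at Day 28 only. Adding counts across sections is also unsafe: Section 8.2 counts deaths up to study day 31 for its Day 28 rate, whereas Section 8.3.2 excludes deaths before the visit.

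Two stronger readings are tempting and not supported. A reader might infer that a drug which keeps ventilated patients alive will look worse here. That requires f above the threshold. Patients ventilated at entry may be off invasive support by Day 28 or Day 60, in which case the shift favours the drug, and the SAP gives no rates to settle it. A reader might also infer that the plan lacks a Day 28 comparison that counts deaths; Section 8.1 shows otherwise.

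It is also fair to note that dead or invasively ventilated has a blind spot. In the last row of the main illustration it is 40% in both arms despite five fewer deaths, so it must be read with mortality.

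**Conclusion.** The point holds in a limited form. The percentages in Section 8.3.2 are conditional on survival and known status, and they are not comparable between arms if mortality differs. The direction of distortion is unknown. Under the assumed main rates the survivor-only figure moves from 14.3% to somewhere between 13.3% and 20.0% for five deaths averted per 100; the wider range above shows the same two-way behaviour. All of these sizes rest on assumed rates.

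The primary, key secondary and Section 8.3.5 results are unaffected. At Day 28 this is a matter of presentation. At Day 60 there is a real gap, because no other specified table shows invasive ventilation. The wording of the exclusion also needs to be tied to each visit.

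**What to change.** - Delete the exclusion sentence in Section 8.3.2.
- Use the mITT set as denominator at each visit; at Day 60, use the mITT patients for whom Day 60 follow-up was planned, and state that number.
- Show mutually exclusive rows: died by that visit, invasive, non-invasive or high flow, none, unknown. The schedule has no oxygenation and ventilation assessment at Day 60, so the Day 60 rows would come from clinical status, which is collected then.
- Describe dead or on invasive ventilation at Day 60, next to Day 60 mortality. No new Day 28 comparison is needed.
- If a survivor-only percentage is kept, label it as conditional on being alive with known status, define the exclusion separately for Day 28 and Day 60, and refer the reader to Sections 8.2 and 8.3.5.

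The cost is a revised table shell and its programming, with no new data. Because the Addendum was written after unblinding, the change should be recorded there as a post-unblinding addition.

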#### **Subgroup analyses :**

Respiratory support will be described by baseline sTREM-1 level (above or equal to the median vs below).

### **8.3.3. Hospital Free Survival at day 28**

The number and percentage of patients alive and not hospitalized at Day 28 will be described by treatment overall and by baseline clinical status. Patients withdrawn alive before Day 28 and without any information on survival/hospitalization status on or after Day 28 will be considered as unknown.

#### **Subgroup analyses :**

Hospitalization free survival at day 28 will be described by baseline sTREM-1 level (above or equal to the median vs below).

### **8.3.4. Sustained remission**

The number and percentage of patients alive and not hospitalized at Day 60 will be described by treatment overall and by baseline clinical status. Patients withdrawn alive before Day 60 and without any information on survival/hospitalization status on or after Day 60 will be considered as unknown.

#### **Subgroup analyses :**

Sustained remission will be described by baseline sTREM-1 level (above or equal to the median vs below).

### **8.3.5. Alive Free of Respiratory Support at Day 28 and at Day 60**

The number and percentage of patients alive and free of any respiratory support (all ventilation types listed in section 8.3.2) at Day 28 and Day 60 will be described by treatment overall and by baseline clinical status. Patients withdrawn alive before Day 28/60 and without any information on survival/clinical status on or after Day 28/60 will be considered as unknown.

#### **Subgroup analyses :**

The number and percentage of patients alive and free of respiratory support at day 28 and Day 60 will be described by baseline sTREM-1 level (above or equal to the median vs below).

## 8.4. Evaluation of the optimal treatment population

The baseline sTREM-1 level and other clinical characteristics will be investigated in order to identify which patients are most likely to respond nangiotide therapy. The best cut-off value for baseline sTREM-1 as a predictive biomarker will be determined based on clinically relevant outcomes which may include but are **not** limited to clinical status, all cause mortality at day 28 and day 60, other clinical outcomes at day 28 and day 60.

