### **4.2. Sample Size**

A total of 370 patients were planned to be enrolled at end of part 2.

Due primarily to a low enrolment rate as a consequence of the low proportion of eligible COVID-19 patients requiring admission to intensive care, the study was terminated early with a sample size of 220 patients.

Safety, Efficacy futility on clinical status 7-point ordinal scale and mortality at Day 28 were analyzed by the DMC after 130 (60 from part 1 and 70 from part 2) patients had completed the 28-day period after randomization (refer to DMC SAP).

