### **4.3. Randomization, Stratification, and Blinding**

#### **4.3.1. Randomization**

The randomization scheme will be generated by an independent statistician who is not part of the study team. A randomization number will be assigned to each patient. The randomization scheme will be generated by a block randomization scheme.

In stage one part 1 of the study, eligible patients were randomized in a 1:1 ratio into 1 of the 2 treatment arms (20 first patients). In stage 2 part 1 of the study, patients were allocated to nangibotide treatment or placebo in a 3:1 ratio resulting in 20 subjects to be randomized on Placebo and 40 subjects randomized on nangibotide at the end of part 1. In part 2 eligible patients will be randomized in a 1:1 ratio into 1 of the 2 treatment arms.

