### **3.3. Survival at Day 28 and Day 60**

As planned in the protocol version 8.0, in sensitivity analyses of mortality at Day 28 and Day 60, a log-rank test stratified by baseline clinical status will be used to compare the treatment arms. In addition, a Proportional Hazard Cox model adjusting for treatment, baseline clinical status will be fitted to estimate the treatment effect expressed in terms of a hazard ratio with the 95% CI and p-value for Survival at Day 28 and Day 60. Survival curves will be produced. These analyses will be performed overall, for patients with baseline sTREM-1 below the median and for patients with baseline sTREM-1 equal or above the median separately.

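### SAP section 8.4 selects a best sTREM-1 cut-off from an open list of outcomes with no selection rule or correction, and no planned analysis tests whether sTREM-1 modifies the treatment effect

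*SAP*

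**What the plan says.** Section 8.4 sets two aims. One is a screen: "The baseline sTREM-1 level and other clinical characteristics will be investigated in order to identify which patients are most likely to respond" to nangibotide. The other is a threshold: "The best cut-off value for baseline sTREM-1 as a predictive biomarker will be determined based on clinically relevant outcomes". The outcomes listed are clinical status, then "all cause mortality at day 28 and day 60, other clinical outcomes at day 28 and day 60", introduced by wording that makes the list non-exhaustive. The section gives no model, candidate cut-offs, selection criterion, validation step or independent sample.

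The other sTREM-1 analyses use a fixed split at the median. For the primary endpoint, section 8.1 says: "The same analysis will be conducted in patients with a sTREM-1 above the median value at baseline vs below". Its sensitivity analyses and the mortality analyses in section 8.2 follow the same pattern. SAP Addendum section 3.3 does so for the log-rank test and Cox model: "These analyses will be performed overall, for patients with baseline sTREM-1 below the median and for patients with baseline sTREM-1 equal or above the median". Here too, each half is analysed on its own.

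The only interaction mentioned is in section 9.4. It concerns co-administered immunomodulatory drugs, not sTREM-1.

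**The concern.** A biomarker is predictive when the treatment effect differs by its level, which is an interaction. Separate tests above and below the median do not address that: one half can reach nominal significance and the other miss it when the true effect is the same in both.

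Section 8.4 adds a selection problem. A cut-off picked because it looks best carries an effect estimate that is biased upward on average, and the open outcome list widens the choice. As worded, the section always returns a best value, even if sTREM-1 modifies nothing. At stake is the credibility of any statement from this trial that a given sTREM-1 level identifies responders.

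**Working it through.** **Inputs from the SAP.** Section 4.2: "the study was terminated early with a sample size of 220 patients". Section 4.3.1: "20 subjects to be randomized on Placebo and 40 subjects randomized on nangibotide at the end of part 1", then 1:1 in part 2. Part 2 therefore contributes 220 - 60 = 160 patients, 80 per arm, giving about 40 + 80 = 120 nangibotide and 20 + 80 = 100 placebo.

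**Check of the plan's own figures.** Section 8.4 states none. The nearest are the effective size of about 210 and the nominal alpha of 0.003303 in section 4.1.
- With effective n = 4ab/(a+b), part 1 gives 20 (10:10) + 30 (30:10) = 50, and 50 + 160 = 210.
- Lan-DeMets O'Brien-Fleming spending with looks at 120/360 and 210/360 gives 0.003303.

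Both reproduce. They confirm the sample-size and allocation inputs but do not bear on section 8.4.

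**Inputs assumed because the SAP gives none.** Number of cut-offs, number of outcomes, correlation between outcomes, event rates and power.

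**Step 1: cut-off selection under no effect.** Simulated trials of 120 vs 100 patients; 17 cut-offs from the 10th to the 90th percentile in steps of 5; z test among patients above each cut-off; a hit is any one-sided p < 0.025 in favour of nangibotide.

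| Outcomes examined | Chance of at least one hit |
|---|---|
| One | about 10% |
| Five, correlation 0.9 | about 19% |
| Five, correlation 0.6 | about 30% |
| Five, correlation 0.3 | about 36% |

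Part of this is multiplicity of outcomes rather than of cut-offs: five outcomes at correlation 0.6 with no cut-off search already give 8-9%.

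**Step 2: size of the selected effect under no effect.** With 25% Day 28 mortality assumed, and depending on the cut-off grid and on whether sTREM-1 is prognostic, the most favourable mortality difference above a cut-off has a median of about -6 to -12 percentage points. It reaches about -18 to -32 points in one trial in ten.

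**Step 3: discordant halves when the effect is identical.** If the overall z has mean m, each half has mean m/√2. With p = P(Z > 1.96 - m/√2), the chance that exactly one half is significant is 2p(1 - p).
- 10% overall power: m = 0.678, p = 0.069, result 13%.
- 50%: m = 1.96, p = 0.283, result 41%.
- 80%: m = 2.80, p = 0.508, result 50%.

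**Step 4: would an interaction test alone suffice?** At the fixed median with one outcome, its false-positive rate is about 5% (two-sided). If a nominal subgroup difference is sought over 7 to 33 cut-offs, the rate is 19-36% with one outcome and 46-74% with six. The search itself must be fixed in advance or adjusted for.

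**The case against.** The strongest reply is section 4.1. It calls the stopped trial exploratory, treats every endpoint except the primary as exploratory, and says the same of secondary p-values. Section 8.4 names no test, p-value or success claim. The median split was set in a SAP approved before unblinding, so it is not itself the product of a search. All of this stands, and the primary type I error is unaffected. But an exploratory label does not correct a selection-biased estimate or turn two split p-values into evidence of effect modification. Section 8.4 also sits outside section 8.3, which carries the exploratory title, and has no caveat of its own.

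Some stronger readings are tempting but not supported:
- A reader might infer that a false responder group is likely. For benefit above a cut-off, the figures here stay below one half. Only the broadest count (any nominal subgroup difference, six outcomes) passes it, and that rests on inputs the SAP does not state.
- A reader might infer that nearly every efficacy endpoint is tested within each half. Section 8.3 is descriptive only, and Addendum sections 3.4 and 3.5 are displays and descriptive summaries. Inferential splits are confined to clinical status, mortality and survival.
- A reader might infer that section 8.4 decides whom a later trial enrols. It mentions no later trial.

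That cut-offs will be compared is itself an inference from the choice of a best value. It is a natural one, but no algorithm is stated.

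**Conclusion.** The point holds in this form: section 8.4 promises a predictive cut-off without a selection rule, a correction for selection or the option of finding none, and no analysis in the SAP or its Addendum estimates the treatment-by-sTREM-1 interaction. Followed as written, the plan yields a cut-off whose apparent effect is biased upward on average, together with split results that cannot show whether the effect differs.

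The inflation is material but depends on assumptions. A nominal 2.5% error becomes about 10% with one outcome and 19-36% with five, given 17 cut-offs and correlations from 0.9 to 0.3. Discordant halves under an identical effect occur in 13-50% of trials for overall power between 10% and 80%. The number analysed could be slightly below 220, because efficacy uses the mITT set. The flaw lies in the predictive conclusion, not in the primary test.

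**What to change.** 1. Beside each inferential median-split result (clinical status, mortality, survival), report the treatment-by-sTREM-1 interaction estimate with its 95% CI.
2. In section 8.4, make the 7-point clinical status at Day 28 the single lead outcome. Model treatment by continuous log(sTREM-1) in the ordinal logistic model adjusted for baseline clinical status.
3. Report any cut-off only with a selection-corrected effect, by bootstrap optimism correction, cross-validation, or a permutation or max-statistic adjustment. Allow the conclusion that no cut-off is supported.
4. State in section 8.4 itself that the result is hypothesis-generating.

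The cost is a few extra models on existing data and, usually, a smaller reported subgroup effect. Interaction power is modest. With 25% mortality and 60 vs 50 patients in each half, the standard error of the difference between halves is √[2 × 0.25 × 0.75 × (1/60 + 1/50)] = 0.117. Power is then about 13%, 40% and 73% for differences of 10, 20 and 30 percentage points. A non-significant interaction would often be uninformative, so the estimate and its interval should carry the interpretation, not the p-value.
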